R-AN	Training session to habituate to the testing environment	A vs. B, A vs. C, A vs. D, B vs. C, B vs. D, C vs. D	A vs. B, A vs. C, A vs. D, B vs. C, B vs. D, C vs. D
C-AN			
U-CT			
N-CT			
R-BN			
C-BN			

*A, B, C, D, samples of ice cream with a high-/low-sweet and high-/low-fat taste. The order of the paired samples and conditions (swallow and spit) will be randomized. R-AN, recovered anorectic; C-AN, currently ill anorectic; U-CT, underweight control; N-CT, normal weight control; R-BN, recovered bulimic; C-BN, currently ill bulimic. R-AN and R-BN will be assessed at discharge*.

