### Study design

The present international and multi-center research uses a quasi-experimental, cross-sectional design with concurrent controls aims at comparing gustatory perception and hedonics of taste among six groups of participants: R-AN, C-AN, U-CT, N-CT, R-BN, and C-BN, under two counterbalanced conditions of testing: sip-and-spit vs. swallow test condition. The use of a rigorous quasi-experimental design with a well-established type of psychopathology represents an important approach in the experimental psychopathology literature (Zvolensky et al., 2013), particularly in the context of eating disorders for both ethical and pragmatic reasons. However, the limitations are related to the lack of random assignment into groups, which leads to non-equal test groups, which can limit the generalizability of the results to a larger population. In order to reduce the impact of this limitation, threats to validity will be minimized controlling the following factors: comorbidity, stage-of-illness, age-at-onset, duration of illness and time in treatment, depressive mood, craving for food, biased cognitions about weight, current hunger, thirst and food familiarity. In addition, age-matched and weight-matched controls (to the extent possible) will be included in the research design to increase the chances of finding differences between groups. Additional controls by limiting our inclusion criteria are not envisaged as this would make it even more difficult to obtain samples of adequate size (therefore reducing statistical power) and limiting the generalizability (and hence the external validity) of the study protocol.

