#### Data processing

In study 1, three direct measures will be derived from the response data of the 2AFC procedure using the SDT (Hautus et al., 2009): the unaffected sensory sensitivity measure (d′) and the two most popular measures of response bias (C and ß). Specifically, the SDT measures will be calculated following Stanislaw and Todorov's (1999) mathematical formulae, with d′ = [z(H)-z(F)]/√2 and z(H) and z(F) are transformations of the hit and false alarm rates to inverse z-scores; calculated in Excel as DPRIME = NORMSINV(H)-NORMSINV(F). Since the more sensitive is an individual the larger the value of d′, an individual who cannot discriminate levels of sweetness or fatness will have a d′ = 0. By contrast, the measure of response bias based directly on cognitive strategy will be calculated in Excel as C = −(NORMSINV(H)+NORMSINV(F))/2. Response bias measures reflect subject's willingness to report that a sensory attribute is present. For instance, while *C* = 0 refers to an unbiased response, a *C* > 0 indicates that the participant has a conservative response bias (i.e., higher likelihood of responding “The higher level of sweetness/fatness is not present” across all food samples). Conversely, a *C* < 0 indicates the participant has a liberal response bias (i.e., a bias toward responding “The higher level of sweetness/fatness is present” across all food samples). Finally, the second measure of response bias will be calculated in Excel as BETA = EXP((NORMSINV(F)^2^−NORMSINV(H)^2^)/2. Considering ß, the neutral point is ß = 1, while ß > 1 reflects a strict criterion (i.e., tendency to say “absent”) and ß < 1 reflects a lax criterion (i.e., tendency to say “present”).

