#### Planned analysis

Analyses will be adjusted for covariates, namely the scores of EDE-Q, BDI-II, FCQ-T-Reduced, TSF-T-Reduced, and hunger and thirst levels. Additional covariates can be added to the model if necessary. In study 1, the procedure for computing the variance of d′, confidence intervals for d', chi-square tests of significance for d′ and comparisons of multiples d′s among groups across two testing conditions will be performed for sweetness, creaminess and caloric content scores according to the Bi et al. (1997) and Bi (2008) approach. Analogous to d′, confidence intervals, hypothesis tests and multiple comparisons for C and ß will be constructed according to Kadlec's (1999) approach.

In study 2, differences in T–I parameters (Imax, Tmax, AUC), self-ratings (hedonic, familiarity) and intensity of facial expressions (emotion, valence and actions units), as well as the cardiovascular, electrodermal and facial electromyographic outcomes, will be analyzed using mixed, three-way factorial ANOVAs with group (six levels) as between-subjects and testing condition (swallowing vs. sip-and-spit) and food sample (four levels) as within-subjects' factors. Additionally, a time series emotional analysis for assessing emotional responses to beverages will be applied to automated facial expression data using the Wilcoxon signed-rank test (Crist et al., 2016) if more sensitive analysis are needed to detect differences between groups. Outcome variables will be checked for normal distribution. Note that linear mixed models to analyse the data can be envisaged to have more statistical power to detect actually existing study effects and to lead to less biased results in the case that the intraclass correlation coefficient and the design effect show dependency in the data (Hox, 1998). Statistical analyses will be conducted using SPSS (IBM, SPSS; Version 23.0, Chicago, IL, USA). Descriptive statistics will be presented using Mean ± *SD* for all continuous variables.

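### Study 1 gives two formulas for d′ that differ by √2; the Excel rule overstates d′ and its confidence limits by 41% for a two-alternative forced-choice task

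*Protocol article*

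**What the plan says.** Table 2 of the protocol article lists d′, C and ß as primary outcomes of Study 1. The Data processing section states that "three direct measures will be derived from the response data of the 2AFC procedure using the SDT". It then defines sensitivity "with d′ = [z(H)-z(F)]/√2 and z(H) and z(F) are transformations of the hit and false alarm rates", and ends the same sentence by saying that it is "calculated in Excel as DPRIME = NORMSINV(H)-NORMSINV(F"), with no √2. It describes d′ as belonging to one person: "Since the more sensitive is an individual the larger the value of d"′.

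The Planned analysis section takes the variance of d′ and its confidence intervals from cited methods, and says that "chi-square tests of significance for d′ and comparisons of multiples d′s among groups across two testing conditions will be performed". The attributes it names are caloric content, creaminess and sweetness. It does not say whether d′ is computed per woman or from choices pooled over women.

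Table 3 lists the pairs for each condition as "A vs. B, A vs. C, A vs. D, B vs. C, B vs. D, C vs. D". The number of replicates is not stated. The Study design section has every group tested "under two counterbalanced conditions of testing: sip-and-spit vs. swallow test condition".

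**The concern.** A definition and its spreadsheet command should return the same number, and here they do not. The command is the yes/no form of d′, while the task is forced choice. Whoever codes the analysis from this section must choose one, and the choice sets the scale of a primary outcome.

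The absolute value of d′, its confidence limits and any comparison with other 2AFC work are at stake. The expected-results section predicts that d′ will be high as well as similar across groups, and high is a statement about the absolute scale. A second risk is that d′ comes from one rule and its variance from a formula written for the other, since the variance is taken from separately cited methods.

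**Working it through.** **Inputs.** The two expressions for d′ (Data processing); the 2AFC task (Data processing and Procedure); six pairs per condition (Table 3); two conditions per woman (Study design); alpha 0.05 and 80 women per study in groups of 15, 15, 10, 10, 15 and 15 (Sample size calculation). Trials per woman, between-woman variation and intraclass correlation (ICC) are not given, so they are assumptions below.

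**1. The two rules side by side.** Text rule: (z(H) − z(F))/√2. Excel rule: z(H) − z(F).

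| H | F | Excel rule | Text rule | Ratio |
|---|---|---|---|---|
| 0.69 | 0.31 | 0.992 | 0.701 | 1.414 |
| 0.80 | 0.20 | 1.683 | 1.190 | 1.414 |
| 0.80 | 0.30 | 1.366 | 0.966 | 1.414 |
| 0.90 | 0.10 | 2.563 | 1.812 | 1.414 |

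The ratio is √2 wherever d′ is not zero, an excess of 41%. The value for no discrimination, d′ = 0, is the same under both.

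**2. Which rule fits the task.** In unbiased 2AFC, H = Φ(d′/√2) and F = 1 − H, so z(H) − z(F) = √2·d′. With true d′ = 1, H = 0.760 and F = 0.240. The text rule returns 1.00 and the Excel rule 1.41. The text rule is the 2AFC one.

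**3. Effect on the tests.** Multiplying every d′ by √2 multiplies its variance by 2. A chi-square of the form Σ(d′ − mean)²/variance is then unchanged, and so are its p-values. If d′ is on the Excel scale but the variance is on the 2AFC scale, the statistic doubles:

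- 1 df: P(χ² > 3.84/2) = 0.166.
- 5 df (six groups): P(χ² > 11.07/2) = 0.354. A simulation of the six groups with 6 choices per woman gave 0.32.

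**4. Rates of 0 or 1, if d′ is per woman.** NORMSINV fails at 0 and 1. The samples form a 2 × 2 of sweetness and fat, so of the six pairs only 2 × 2 = 4 differ in any one attribute. With pc = Φ(d′/√2) and n trials per presentation order, the chance that H or F is 0 or 1 is 1 − (1 − pcⁿ − (1 − pc)ⁿ)².

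- n = 2 (assumes no replicates): 87% at d′ = 1 and 98% at d′ = 2.
- n = 6 (assumes Table 3 run three times): 35% at d′ = 1 and 85% at d′ = 2.

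A log-linear correction makes every value finite. It does not add information: with n = 2 the largest corrected rate is (2 + 0.5)/(2 + 1) = 0.833, so d′ cannot exceed (0.967 + 0.967)/1.414 = 1.37.

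**5. Dependence, if choices are pooled over women.** With m choices per woman, the design effect is 1 + (m − 1)·ICC. The type I error of a 5-df group test that ignores it is:

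| Choices per woman | ICC 0.05 | ICC 0.10 | ICC 0.20 |
|---|---|---|---|
| 6 | 0.115 | 0.194 | 0.354 |
| 12 | 0.21 | 0.38 | 0.63 |

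A simulation with 6 choices, mean d′ = 1 and a between-woman SD of d′ of 0, 0.5 and 1.0 gave 0.04, 0.11 and 0.33. For spit versus swallow in the same women the error runs the other way: ignoring a correlation of 0.2 or 0.4 lowers a 5% test to 0.028 or 0.011.

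**The case against.** The strongest reply is that this is a slip in one spreadsheet expression beside a correct 2AFC definition. The nearby expression for ß has an unbalanced bracket, so loose transcription is plausible, and the article does not prove which line will be run. That is fair. It limits the point to a contradiction that must be resolved; it does not remove it, because both rules are printed as the rule for d′.

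A reader might go on to infer that the error rates of the d′ tests are wrong. The article does not support this. A common √2 cancels when the variance is on the same scale, and rescaling all groups alike cannot change whether they are similar, which is what H1 claims for sensory performance. The 17% and 35% need a mismatch of scales that the article nowhere describes.

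A reader might also infer that the chi-square comparison treats repeated choices by one woman as independent. The Planned analysis section never says that choices are pooled or d′s independent; it points to cited methods that are not at hand, and the Data processing section speaks of an individual's d′. The article leaves the unit of analysis open, and an article may leave that to the full plan. So dependence is a conditional point only.

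Finally, the figures in steps 4 and 5 belong to different readings and different assumed trial counts, and should not be added together.

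**Conclusion.** The contradiction is certain and follows from the article alone. Run as printed, the Excel rule overstates d′ and its confidence limits by 41% for this task. Group and condition tests are unchanged if the variance matches the rule used.

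Two further points hold conditionally. If d′ is computed per woman, rates of 0 or 1 will be common unless each pair is replicated many times, and no correction is stated. If choices are pooled over women, ignoring repetition inflates the group test and makes the spit/swallow test conservative. The size depends on between-woman variation that the article does not give. The inflation would produce false group differences in d′, which works against the similarity that H1 predicts.

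**What to change.** 1. State one rule: DPRIME = (NORMSINV(H)-NORMSINV(F))/SQRT(2). Use the matching 2AFC variance for its confidence limits and chi-square tests.
2. State whether d′ is computed per woman or from pooled choices, and how often each pair is replicated.
3. If per woman, apply the log-linear correction (add 0.5 to each count and 1 to each number of trials) to every participant, including those whose rates are not extreme.
4. If pooled, allow for repeated choices and for the spit/swallow pairing. One way is a probit mixed model of the response given, with a presentation-order term that carries d′, an intercept that carries bias, group and condition effects on both, and participant random effects on both. With order coded ±1, the order coefficient times √2 is d′.

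Do not model correct choice alone. Bias lowers the proportion correct in 2AFC, and H1 predicts that bias differs between groups and conditions. With true d′ = 1.5 (d′/√2 = 1.061) and a criterion shift of 0.5, the proportion correct is (Φ(0.561) + Φ(1.561))/2 = 0.827, and √2·z(0.827) gives 1.33. A difference in bias would then look like a difference in d′, and such a model yields neither C nor ß.

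Item 1 is a one-line change plus a check of the variance formula. The others need some wording and programming. No new data are needed.

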H1: If perceptual disturbances in AN and BN are related to biased cognitions about gaining weight rather than to gustatory deficits or BMI, then AN and BN patients should respond with similar sensory performance but higher response bias scores in a discrimination test, (1) compared to non-ED underweight, normal-weight and illness-recovered controls, and (2) during a swallowing compared with a sip-and-spit condition.H2: If fear of weight-gain in restricting-type AN elicits taste aversion, then facial electromyographical, facial expression, and autonomic and subjective correlates of disgust (Kappas, 2003; Kreibig, 2010) while tasting high-sweet and high-fat foods should be observed compared to (1) stimuli of low-sweet and low-fat foods; (2) non-ED underweight, normal-weight, illness-recovered controls and (3) BN patients; and (4) especially during the swallowing compared with the sip-and-spit condition.H3: If avoidance of energy-rich foods in BN reflects a cognitive preoccupation about the increased liking of very sweet tastes associated with gaining weight, then facial electromyographical, facial expression, and autonomic and subjective correlates of pleasure (Kappas, 2003; Kreibig, 2010) while tasting high-sweet foods should be observed compared to (1) fat and low-sweet stimuli; (2) non-ED underweight, normal-weight, illness-recovered controls and (3) restrictive-type AN; and (4) no differences between swallowing and sip-and-spit conditions.

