The experimental session will be composed of assessments of thirst and hunger levels, the Thought-Shape Fusion Body State Scale (TSF-B state) and Brief Mood Scale (BMS) questionnaire, a training session to habituate to the testing environment and apparatus, and either the discrimination of two-alternative forced-choice (2AFC) test in study 1 or multiple-sip temporal-liking (MSTL) with taste reactivity (TR) task in study 2. Each experimental session will take around 1.5 h. Concerning the first study (Table 3), the 2AFC test with signal detection theory (SDT) analysis will be used as it provides a high level of power for small food differences and low levels of response bias (Hautus et al., 2009). On the one hand, the 2AFC test is a psychophysical method in which participants are required to select the one of two food samples, which represents the specified attribute best (e.g., the sweeter one). On the other hand, SDT is a sophisticated tool that permits to understand the information processing that takes place in the brain during sensory discrimination testing, providing an accurate index of perceived sensory differences and efficient characterization of cognitive strategy. Therefore, SDT is critical for investigating maladaptive cognitions involved in the processing of received taste information, which affects sensory testing (Smeets et al., 2008). Furthermore, whether and how much gustatory performance depends on low BMI or psychopathology will be examined including under- and normal-weight controls and patients at different stages of the disorder (currently-ill vs. recovered). Finally, in addition to the sip-and-spit condition, a swallow test condition will be included (Eiber et al., 2002) to enhance cognitive bias toward weigh gain underlying the fear of swallowing and quantify the impact of these biased cognitions on gustatory performance. The 2AFC task will be conducted using the SIPM™ software (Sussex Ingestion Pattern Monitoring, version 2.0.11), in which pairs of two samples (with varying levels of sweetness and fatness), presented simultaneously at each trial, are judged in terms of taste identity and intensity (see Table 2).

**Table 3 T3:** Experimental design of the study 1.

**Group**	**Pre-test**	**Test: two-alternative forced-choice task**	
		**Spit condition**	**Swallowed condition**

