### The expected results

Concerning the study 1, the main results to be expected are that a different and reduced C (*C* < 0) and (ß < 1) are expected in currently-ill AN and BN patients compared to non-ED underweight, normal-weight and illness-recovered controls, and during a swallowing compared with a sip-and-spit condition. Reduced C and ß-values would show a response bias to say, “Yes, the gaining weight-related attribute [sweetness, creaminess and caloric content] is present.” By contrast, patients will have a similar high d′ value compared with control groups, which means that all the participants have a good sensory discrimination.

Concerning the study 2, it is mainly predicted that restricting-type AN will show evidence of reduced verbal ratings as well as bodily higher corrugator activity, disgust facial expressions and heart rate acceleration in response to high-sweet and high-fat foods compared to stimuli of low-sweet and low-fat foods; non-ED underweight, normal-weight, illness-recovered controls and BN patients; and especially during the swallowing compared with the sip-and-spit condition. On the other hand, higher zygomatic muscle activity and more smiles expressions in response to very sweet tastes will be expected to observe in BN compared to fat and low-sweet stimuli; non-ED underweight, normal-weight, illness-recovered controls and restrictive-type AN; and no differences between swallowing and sip-and-spit conditions.

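### Study 1 derives C and ß from a pick-one-of-two task but reads them as a yes/no tendency to say the attribute is present; a general bias of that kind cancels in the choice, so the response-bias half of H1 cannot be tested as written

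*Protocol article*

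**What the plan says.** All references are to the Protocol article.

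- **Task.** The Procedure section describes a two-alternative forced-choice (2AFC) test in which "participants are required to select the one of two food samples, which represents the specified attribute best". Samples are shown in simultaneous pairs. Table 3 lists the six pairs of four samples, in the spit and the swallow condition. One stated reason for the method is its "high level of power for small food differences and low levels of response bias".
- **Measures.** Under Data processing, "three direct measures will be derived from the response data of the 2AFC procedure using the SDT": d′, C and ß. Table 2 lists them as primary for Study 1, in the same row as 0–10 ratings of sweetness and fattiness.
- **Meaning given to C and ß.** The same section says that they reflect "willingness to report that a sensory attribute is present". Positive C is read as a leaning towards answering that the higher level is absent, and negative C as a leaning towards answering that it is there. ß is read the same way around a neutral value of 1.
- **Prediction.** H1 expects patients to show "similar sensory performance but higher response bias scores in a discrimination test". The expected results section predicts "a different and reduced C" (below 0), with ß below 1, in currently ill patients, and explains this as a tendency to answer yes for sweetness, creaminess and caloric content.

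**The concern.** The task, the formulas and the interpretation do not fit together. A yes/no criterion can be estimated when each sample is judged singly as having or lacking the attribute. In a forced choice between two samples, the participant says only which has more. The text gives no rule for what counts as a hit or a false alarm in a pair, so it is unclear which H and F enter the formulas, and neither natural scoring yields the quantity described.

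Response bias is the positive half of H1: patients are expected to match controls on d′ and differ on bias. If the bias measure cannot respond to the hypothesised cognition, a null result says nothing about that cognition, and a non-null result may have another source. Pairwise choices alone do not allow the bias to be recovered after the data are in.

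**Working it through.** **Inputs from the protocol (Data processing).** C = −[z(H) + z(F)]/2; ß = exp{[z(F)² − z(H)²]/2}; neutral points C = 0 and ß = 1.

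**Assumptions, not protocol figures.** Equal-variance normal percepts with SD 1; true d′ = 1; a general bias modelled as an upward shift b common to all samples; a position preference modelled as an advantage p for one position.

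**Step 1: the plan's neutral points.** With H = 0.76 and F = 0.24, z(H) = 0.706 and z(F) = −0.706. So C = −(0.706 − 0.706)/2 = 0 and ß = exp(0) = 1. The stated neutral points are reproduced.

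**Step 2: scored correct/incorrect.** Here F = 1 − H, so z(F) = −z(H). Then C = 0 and ß = 1 for every H. This is an identity and carries no information about bias.

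**Step 3: coded by position.** Let a hit be choosing position 1 when the stronger sample is there, and a false alarm choosing position 1 when the weaker one is there. The choice depends on (x1 + b) − (x2 + b) = x1 − x2, so b drops out. With position advantage p:

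- H = Φ[(d′ + p)/√2] and F = Φ[(p − d′)/√2]
- C = −p/√2 and ß = exp(−p·d′)

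Results at d′ = 1, which agree with a simulation of 2,000,000 trials per setting:

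| Setting | H | F | C | ß |
|---|---|---|---|---|
| Common shift b = 0, 0.5, 1 or 2; p = 0 | 0.76 | 0.24 | 0.00 | 1.00 |
| p = 0.3, no general bias | 0.82 | 0.31 | −0.21 | 0.74 |
| p = 0.6, no general bias | 0.87 | 0.39 | −0.42 | 0.55 |
| p = 1.0, no general bias | 0.92 | 0.50 | −0.71 | 0.37 |

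C and ß ignore the hypothesised bias and respond to position preference.

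**Step 4: a cognition acting only on the stronger sample.** A boost of 0.5 or 1 SD to that sample raises d′ (the form with √2) from 1.0 to 1.5 or 2.0 and leaves C = 0 and ß = 1. It appears in the measure that H1 expects to be similar across groups.

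**Step 5: the same common shift with single-sample yes/no answers** (criterion midway, at 0.5).

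| Shift b | C | ß |
|---|---|---|
| 0.5 | −0.50 | 0.61 |
| 1 | −1.00 | 0.37 |
| 2 | −2.00 | 0.14 |

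This is the behaviour that the Data processing and expected results sections describe. It belongs to a different task.

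**Side observation.** Data processing gives d′ once with division by √2 and once, as the spreadsheet formula, without. At H = 0.76 and F = 0.24 these are 1.00 and 1.41. The first form fits 2AFC and the second fits yes/no, which points to the same mixing of two tasks.

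**The case against.** The strongest defence is that the article may not show the whole response format. The Procedure section also says that pairs are judged for identity and intensity. Table 2 puts d′, C and ß in the same row as the 0–10 ratings. Data processing words one response as the higher level not being there. In a 2×2 set of samples, two of the six pairs do not differ on a given attribute, so they could serve as noise trials if such an answer existed. Trial-level scoring is often left to a fuller document.

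This makes another scoring conceivable, but the text does not supply it. The task as described is to pick one sample, and the three measures are stated to come from the 2AFC responses. This is a conflict between things the article does state, so it is more than omitted detail. The defence does mean that the conclusion must be conditional on pick-one responses.

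Two further objections stand:

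- The cancellation is algebra that follows from assuming a uniform shift. The d′ and shift sizes are illustrative.
- Choosing a method for its low response bias does not prove that bias is unmeasurable. It only sits awkwardly with making bias a primary measure.

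**Conclusion.** The point holds, conditional on the pick-one task as described. C and ß from these choices cannot show a general tendency to perceive or report more of the attribute. They are 0 and 1 identically under correct/incorrect scoring. Under position coding they reflect only position preference. The response-bias half of H1 is then not testable by its stated measure, and the error can run either way: a real bias can be missed, or a position preference taken for the predicted liberal bias. This needs settling before data collection.

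Stronger readings are not supported:

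- **C and ß will be 0 and 1 in every group, and power equals alpha.** This is exact only when F = 1 − H. With position coding it holds in expectation and only without a position preference; observed values will also scatter.
- **H1 and the expected results predict opposite effects.** A higher bias score in H1 can mean a bias of greater magnitude, and the signed prediction in the expected results agrees with the scale in Data processing. Because a literally higher C or ß means the opposite bias on that scale, H1 needs rewording, but this is secondary.
- **Study 1 as a whole fails.** The d′ half of H1 is not affected by this point, and neither is Study 2.

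**What to change.** 1. Use the 2AFC choices for d′ only, and do not interpret C or ß from them as a tendency to report the attribute as present.
2. Derive the bias measure from the 0–10 sweetness and fattiness intensity ratings already primary in Table 2, recorded for each sample. Treat high-level samples as signal and low-level samples as noise, and define hits and false alarms accordingly. Compare group, condition and group × condition. An ordinal probit mixed model is one suitable choice among several.
3. Reword H1 to the signed prediction: lower C and ß in currently ill patients.

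**Cost.** No new instrument is needed for sweetness and fattiness, but each sample, not only each pair, must be rated. If each of the six pairs is tasted once (an assumption; repeats are not given) and both samples are rated every time, that is 6 × 2 = 12 ratings per attribute and condition, six from high-level and six from low-level samples. Table 2 does not list a caloric-content rating for Study 1, so one would have to be added if that attribute stays in the prediction. A limitation remains: rating-based bias does not fully separate a changed percept from a changed reporting criterion, and the interpretation of H1 should say so.
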